#### Randomization and RCT design elements

Eligible participants will be randomized by the principal investigator ([name]), who will not be blinded, in order to provide close monitoring of the procedures. The principal investigator will allocate participants sequentially as they are enrolled to either the T or the C group using the minimization algorithm by Pocock and Simon [41] implemented in the R statistical software package [42]. Randomization will be stratified for (1) GA (24-0/7 to 27-6/7 weeks or 28-0/7 to 31-6/7 weeks), to control for potential development differences in response to the intervention and as a proxy for neural injury, and (2) socioeconomic status (SES) (above versus below average SES; based on Hollingshead Index (HI) [36, 43]), to control for potential differences in language outcomes affected by socioeconomic factors. Taking into account ethical considerations and parental preferences, twins and multiples will be assigned to the same group [44]. Families and research and clinical staff will be blinded to the group status. In the unlikely event that a family, research staff, or clinical staff suspect that an infant may not tolerate the speech recording, the principal investigator will reveal the group assignment.

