### Analysis plan

#### Power calculations

We calculated the sample size based on power. The significance level is *p* < 0.05 for all analyses. Power estimates are based on the means, standard deviations, and samples size from an RCT neuroimaging study of preterm neonates that showed a significant effect of a parent-based NICU intervention on diffusion metrics measured at close-to-term age (Cohen’s *d* = 1.03) and developmental outcomes (Cohen’s *d* = 1.77) measured at 9 months AA [56]. Thus, if we assume an effect size that is more conservative than this earlier study, specifically Cohen’s *d* = 1.0, we will have a power of ß = 0.8, if we enroll a sample size of at least 17 participants per group. Therefore, our planned enrollment of 21 participants per group will yield a power of ß = 0.88 to detect an effect size at that level (Cohen’s *d* = 1.0). If our effect size is even smaller than we anticipate, for example, Cohen’s *d* = 0.9, a planned enrollment of 21 per group will still yield a power greater than 0.8 to detect a treatment effect.

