#### Analytic strategy

We anticipate that stratification prior to randomization will result in a close matching of T and C groups on demographic and health variables. Prior to statistical analyses, we will use independent samples t-tests (continuous variables) or chi-square tests (categorical variables) to assess the statistical balance between T and C groups on the basis of GA, sex, SES, clinical complications associated with premature birth, and language exposure during treatment and after hospital discharge. Analyses will use an intention-to-treat strategy [57]. If groups are matched on all variables, we will use independent t-tests (two-tailed) to compare T versus C groups on the primary long-term language outcome and the secondary short-term outcomes that relate to white matter development. Should groups not be balanced, and to account for missing data, we will use linear mixed models: T group as a fixed factor and unmatched or missing variables are random factors. Statistical significance is set at *p* < 0.05. Should an imbalance of twins or multiples occurs, we will perform group analyses including all singletons and one randomly selected twin or multiple from each set [58].

We will perform post hoc univariate and/or non-parametric analyses to determine if neural and clinical outcomes are associated with variations in the dose (i.e., number of hours of maternal speech delivered) or length (i.e., number of nights of delivery) of treatment, controlling for GA and PMA. Post hoc covariance analyses will permit further interpretation of either significant or non-significant treatment effects for short- and long-term neural and language outcomes. We will use multiple regression analyses to predict language outcomes from short-term neural and clinical outcomes, while controlling for group status and measures of language exposure.

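### Siblings always share an arm, but the analysis treats infants as independent unless multiples are unevenly split, which is the wrong trigger for a clustering correction

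*Protocol article*

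**What the plan says.** Three statements in the protocol article bear on this point.

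- **Allocation** (Randomization and RCT design elements): "twins and multiples will be assigned to the same group". For multiples, the family is therefore the allocated unit. Allocation uses Pocock–Simon minimisation on gestational age (GA) and socioeconomic status (SES).
- **Analysis** (Analytic strategy): if the groups match, "we will use independent t-tests (two-tailed) to compare T versus C groups on the primary long-term language outcome". Otherwise the plan uses "linear mixed models: T group as a fixed factor and unmatched or missing variables are random factors". Neither branch names a family term.
- **Multiples** (Analytic strategy): "Should an imbalance of twins or multiples occurs, we will perform group analyses including all singletons and one randomly selected twin or multiple" (one per set). The article does not say what counts as an imbalance, or whether this analysis replaces the all-infant analysis or is added to it.

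The power section counts infants as independent and does not mention multiples. It assumes an effect of "specifically Cohen’s *d* = 1.0" and claims power of 0.8 "if we enroll a sample size of at least 17 participants per group".

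**The concern.** Siblings share a mother (whose recorded voice is the intervention), a household, an SES score and the parent who completes the language questionnaire. Their outcomes are likely to be positively correlated. When correlated infants always sit in the same arm, each adds less information than an independent infant, and an independent t-test understates the standard error of the group difference.

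This does not depend on whether the arms hold equal numbers of multiples. The article acts only on imbalance, so an equal split, which looks like the favourable outcome, is the case with no correction. Because imbalance is undefined, whether the correction applies at all is left to judgement. At stake are the validity of the primary p-value and confidence interval, and the stated power.

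**Working it through.** **1. The plan's own figures.** Two-sided two-sample t-test, alpha 0.05, 1:1, noncentral t:

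| n per arm | d | Recomputed power | Stated |
|---|---|---|---|
| 17 | 1.0 | 0.807 | 0.8 |
| 21 | 1.0 | 0.885 | 0.88 |
| 21 | 0.9 | 0.812 | more than 0.8 |

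The figures reproduce, for independent infants.

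**2. Size of the naive t-test with multiples equally split.** For set sizes m, the design effect is DE = 1 + ICC × (Σm²/Σm − 1). With a share f of infants in twin pairs and the rest singletons, Σm²/Σm = (1 − f) × 1 + f × 2 = 1 + f, so DE = 1 + f × ICC. The naive standard error is about 1/√DE of the true one, and the actual size is about 2 × P(t₄₀ > 2.021/√DE). Both f and ICC are assumptions, because the article gives neither.

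| f | ICC | DE | 2.021/√DE | Size, formula | Size, simulated (5,000 runs) |
|---|---|---|---|---|---|
| 0.2 | 0.5 | 1.10 | 1.927 | 0.061 | 0.060 |
| 0.3 | 0.7 | 1.21 | 1.837 | 0.074 | 0.077 |
| 0.4 | 0.8 | 1.32 | 1.759 | 0.086 | 0.083 |

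A larger simulation (200,000 runs per cell, the same number of twin pairs in each arm of 21) gave 0.066 for 3 pairs per arm at ICC 0.5 and 0.091 for 5 pairs at ICC 0.7. Its extremes were 0.056 (2 pairs, ICC 0.3) and 0.127 (7 pairs, ICC 0.9). The last needs two thirds of infants to be twins. If imbalance means unequal numbers, the article's rule would not fire in any of these cases.

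**3. Effect of minimisation.** The calculation above ignores the balancing on GA and SES. An unadjusted t-test after balancing on prognostic factors is conservative, and siblings share both factors. Simulated Pocock–Simon allocation (assumed biased coin 0.8, pairs kept together, 6,000 runs, Monte Carlo error about 0.003) gave these sizes, where R² is the assumed share of outcome variance explained by the two binary strata:

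| Twin pairs in 42 infants | ICC | R² = 0 | 0.1 | 0.2 | 0.3 |
|---|---|---|---|---|---|
| 4 | 0.5 | 0.064 | 0.054 | 0.040 | 0.029 |
| 6 | 0.7 | 0.074 | 0.055 | 0.046 | 0.037 |
| 8 | 0.8 | 0.082 | 0.079 | 0.056 | 0.046 |

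The R² = 0 column agrees with step 2. As R² rises, the inflation shrinks and can reverse.

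**4. The one-sibling rule.** Three twin pairs per arm leave 21 − 3 = 18 infants per arm: power 0.830 at d = 1.0 and 0.746 at d = 0.9. Two pairs leave 19: 0.851 and 0.770. Simulated type I error under this rule stayed at 0.048 to 0.052.

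**5. What keeping all infants recovers.** Take 3 pairs per arm and ICC 0.5. With equal weights the effective size is 21/1.143 = 18.4 per arm: power 0.838 and 0.756. With optimal weights each pair counts as 2/(1 + 0.5) = 1.33 infants, so 15 + 3 × 1.33 = 19 per arm: power 0.851 and 0.770, if the ICC were known. Most of the shortfall from 0.885 and 0.812 therefore comes from the clustering itself, and the discarding adds a little.

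**The case against.** Four objections deserve an answer.

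- **Inflation is not a fact.** A reader might infer that the primary test is anticonservative. The documents do not support that as a certainty: it needs enrolled multiples and a positive ICC, neither of which is given, and step 3 shows that minimisation with an unadjusted test pushes the other way. This stands. The offset is accidental, however: it depends on an unknown R² and is not a planned safeguard.
- **Intention-to-treat.** A reader might infer that analysing one sibling per set contradicts "Analyses will use an intention-to-treat strategy". That is too strong. The draw does not depend on outcome, adherence or arm; every family stays represented in its assigned arm; the contrast is not biased; and type I error holds near 0.05. The cost is precision and dependence on which sibling is drawn. The wording also does not say that the reduced analysis replaces the full one.
- **The rule may fire often.** If any unequal number of sets counts as imbalance, 6 sets under simple 1:1 allocation split evenly with probability 20/64 = 0.31, and an odd number never does. So how often the uncorrected test applies is unknown. That is a consequence of leaving the trigger undefined, not a defence of it.
- **A family model is fragile here.** With about six informative pairs, the sibling correlation is poorly estimated. This stands, and making the one-sibling rule unconditional would also give valid standard errors.

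**Conclusion.** The concern holds as a wrongly specified rule. Same-arm allocation of siblings calls for a family-aware analysis whether or not multiples are evenly split, and the article supplies a correction only under an undefined imbalance. Since the article states the rule and its trigger, this is not a detail left to a later document.

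The size is conditional. With 20–40% of infants in twin pairs and ICC 0.5–0.8, type I error is about 6–9% before minimisation is considered. If GA and SES explain 10–30% of outcome variance and are left out of the model, the simulated size runs from about 0.03 to 0.08, so the direction of the net error is not established. The one-sibling rule is valid but inefficient, and the efficiency loss is modest. The stated power at "The significance level is *p* < 0.05 for all analyses" holds only for independent infants: at d = 0.9 it falls below 0.8 in every clustered case computed (0.789 at best, with 2 pairs per arm and ICC 0.3).

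**What to change.** - Remove the imbalance trigger and account for siblings in every case.
- Preferably, analyse all randomised infants with a family random intercept and small-sample degrees of freedom (for example Kenward–Roger), or with family-clustered GEE and a small-sample correction.
- Adjust that model for the GA and SES minimisation factors, so that the error rate does not rest on two opposing errors cancelling.
- Keep the one-sibling-per-set analysis as a sensitivity analysis, with the draw made from a pre-set seed.
- State in the power section that its figures assume independent infants, and give a range for plausible twin shares and ICCs.

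**Cost:** changes to the analysis and power wording; recruitment and follow-up are unaffected. The confidence interval will be slightly wider for the clustering, the stated power slightly lower, and the sibling correlation imprecisely estimated from few pairs.

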### Participants

Preterm neonates born and admitted to the LPCH’s NICU at Stanford University will be eligible to participate. To be eligible, neonates must be born between 24-0/7 and 31-6/7 weeks GA (*N* = 42; T: *n* = 21 and C: *n* = 21). All races and ethnicities will be included. However, we will enroll infants whose family’s primary language is English or Spanish, because of our limitations in communicating with families using other languages. The primary language outcome, the CDI: Words and Gestures Questionnaire, will be administered in English or Spanish, as appropriate [37, 38]. Eligible participants must be free of the following adverse outcomes that could potentially confound language and neuroimaging outcomes: (1) congenital anomalies or recognizable malformation syndromes; (2) serious neurological conditions, including active seizure disorders, history of central nervous system infections or hydrocephalus, intraventricular hemorrhage grades III–IV, and cystic periventricular leukomalacia; (3) surgical treatment for necrotizing enterocolitis; (4) small for GA (< 3 percentile) and/or intra-uterine growth restriction; and (5) major sensori-neural hearing loss.

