#### Control variables and covariates

To characterize the sample and ensure balance across groups in analyses for treatment effects, we will prospectively collect the following information from electronic medical records and parent report questionnaires to control for (1) major medical complications associated with prematurity, including GA, birth weight, sex, history of antenatal steroid usage, infection, number of days of intubation and oxygen, and X-ray changes consistent with chronic lung disease; (2) PMA at MRI scan; (3) the number of nights of exposure to study treatment; and (4) sociodemographic factors associated with later language outcomes, including the SES of primary caretakers as measured by the HI [43], the frequency and number of languages spoken by adult and child household members, and number of siblings.

We will also obtain metrics to ensure balance across groups on the basis of the amount of language exposure experienced by infants in their home environments. To collect data on naturalistic maternal/caregiver input during the infancy period, we plan to use the Language ENvironment Analysis (LENA) recording device and software [54]. Families will be asked to perform two full-day (16 h) home LENA voice-recording sessions immediately around the time of the 12 months AA visit for MRI scanning. From this device, we will examine the adult words count measure per hour, normalizing for the length of audio recording, since it is the most accurate measure from LENA at this age when the infants may have limited language production skills [55]. If the groups do not match, we will use this language exposure metric as a covariate in the analyses.

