## Discussion

Despite consistent evidence linking preterm birth to delays in language development, few clinical interventions for promoting healthy language development currently exist. To our knowledge, the present RCT is the first designed to assess the impact of increased exposure to maternal speech on long-term language outcomes and white matter brain development. By examining the potential changes induced by increased exposure to maternal speech on white matter connectivity, this RCT may promote changes in infant brain development that may serve as a marker of effective intervention and a precursor of future language development. Therefore, the significance of this RCT resides in that we may be able to prevent neurodevelopmental delays before they manifest and thus move the child toward favorable developmental trajectories, by intervening early in the hospital nursery. The ultimate significance of the proposed research will be to establish the nature and timing of language interventions for improving language and neural outcomes in preterm infants.

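### The exploratory regression of language on the neonatal brain measure names group and language exposure as controls but not gestational age or age at scan, so immaturity may confound the association

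*Protocol article*

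**What the plan says.** The last sentence of the Analytic strategy section reads: "We will use multiple regression analyses to predict language outcomes from short-term neural and clinical outcomes, while controlling for group status and measures of language". The last item is the infants' exposure to language. GA, PMA at scan and socioeconomic status (SES) are not among the named controls.

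Earlier in the same paragraph, the post hoc analysis relating neural and clinical outcomes to dose or "length (i.e., number of nights of delivery) of treatment, controlling for GA and PMA" does name GA and PMA.

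Three other places bear on the point:

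- Randomization and RCT design elements: GA is a stratification factor "to control for potential development differences in response to the intervention and as a proxy for neural injury".
- Control variables and covariates: GA, PMA at the MRI scan and SES are all collected. The stated purpose is "To characterize the sample and ensure balance across groups in analyses for treatment effects".
- Discussion: white matter changes "may serve as a marker of effective intervention and a precursor of future language development".

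**The concern.** Randomisation protects the comparison of the two arms. It does not protect an association between two measurements taken on the same infants. Stratifying on GA balances it between arms but leaves its variation within each arm, and a term for group does not remove that variation. The Participants section admits a wide range: "neonates must be born between 24-0/7 and 31-6/7 weeks GA".

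On the protocol's own premises, the less mature infants may have both less developed white matter and lower language scores. The regression could then give a significant MD coefficient with no contribution from white matter beyond gestation. At stake is the reading of MD as an early sign of later language. The Power calculations section sets p < 0.05 for all analyses, so a significant coefficient here would probably be taken as support for that reading.

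**Working it through.** **The plan's own figures.** No stated figure concerns this regression. The stated power for the two-arm comparison does reproduce: a two-sided t-test with 21 per group and d = 1.0 gives 0.885, against 0.88 in the article. That figure is not in question.

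**Inputs.**

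- From the article: N = 42 (21 per group), two-sided alpha 0.05, and group and language exposure as controls.
- Assumed: correlation *a* between GA and MD, and correlation *b* between GA and language, both in absolute value. There is no direct link between MD and language, and GA is unrelated to group and exposure.

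**Step 1: the association induced by leaving GA out.** If GA is the only connection, the MD-language correlation is *a* × *b* in size.

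**Step 2: how often that is significant.** With Fisher's z and two covariates partialled out, the standard error is 1/√(42 − 2 − 3) = 1/√37 = 0.1644. Put δ = atanh(*ab*)/0.1644. The rejection rate is then Φ(δ − 1.96) + Φ(−δ − 1.96).

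| *a* = *b* | *ab* | atanh(*ab*) | δ | Rejection rate | Simulated, GA omitted |
|---|---|---|---|---|---|
| 0.2 | 0.04 | 0.0400 | 0.243 | 5.7% | 5.7% |
| 0.3 | 0.09 | 0.0902 | 0.549 | 8.5% | 8.3% to 9% |
| 0.4 | 0.16 | 0.1614 | 0.982 | 16.6% | 16.9% to 18% |
| 0.5 | 0.25 | 0.2554 | 1.554 | 34.2% | 34.4% to 35.4% |

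The last column comes from least-squares fits of language on MD, group and exposure, with 6,000 simulated trials per setting. Its ranges are the spread over separate runs. What matters is the product *ab*: for example, *a* = 0.5 with *b* = 0.3 gives 15.5%.

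**Step 3: add GA.** With GA as a further term, the simulated rate returns to between 4.6% and 5.2% for correlations of 0.2 to 0.5.

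**Step 4: allow for the clinical predictors.** The planned model also contains short-term clinical outcomes, which the article does not define here. Suppose one of them correlates with GA at 0.6 or at 0.8 (assumed), and GA itself is still omitted:

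| *a* = *b* | No clinical predictor | Clinical–GA correlation 0.6 | Clinical–GA correlation 0.8 |
|---|---|---|---|
| 0.3 | 8% | 6.5% | 5% |
| 0.4 | 16% | 10% | 7% |
| 0.5 | 34% | 20% | 10% |

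A clinical predictor that tracks immaturity removes much of the excess. At the higher correlations it does not remove all of it.

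**The case against.** The strongest reply is that little depends on this sentence. Both aims and both outcome definitions are comparisons of treatment with control, and the regression comes last in a paragraph of post hoc analyses. A journal article may also leave the covariates of an exploratory model to the analysis plan, and the list under Control variables and covariates could be read generously as covering every analysis. The first part stands: no treatment conclusion depends on this regression. The second does not fully answer the point. The sentence does name an adjustment set, the neighbouring analysis names a different one, and the general list is tied to treatment-effect analyses.

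Three further objections also limit the claim:

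- **Size.** The correlations are assumptions, and near 0.2 the inflation is negligible. The white matter evidence in the Background compares preterm with term-born infants, not a gradient within 24 to 31 weeks. The exclusions for severe injury and the use of adjusted age could weaken that gradient. A reader might take 35% as the error rate of the planned model. It is not, because the planned model also holds clinical predictors.
- **The Discussion.** A reader might infer that the sponsor will declare MD a precursor of language on the strength of this coefficient. The Discussion is hedged, speaks of changes induced by the intervention, and nowhere cites this regression. The link is an inference.
- **The other covariates.** A reader might treat PMA at scan and SES as confounders on a par with GA. The document does not link SES to MD. PMA at scan, planned at about 36 to 38 weeks, confounds only if scan timing tracks maturity or illness. Otherwise leaving it out mainly adds noise to MD.

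**Conclusion.** The point holds in a limited form. Followed as written, the regression leaves a plausible common cause, GA, uncontrolled, and it is inconsistent with the analysis beside it. For assumed GA correlations of 0.2 to 0.5 with each variable and no direct link, a nominal 5% test of MD rejects in about 6% to 35% of trials when only group and exposure are controlled. The excess is smaller to the extent that the clinical predictors carry immaturity. Confounding is possible here, not demonstrated. It bears on the exploratory brain-language association alone. The randomised comparisons of language and of MD are untouched.

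**What to change.** In the Analytic strategy section, add GA (as a continuous variable) and PMA at the neonatal scan to the controls for this regression, in line with the dose and length analysis. Base any statement that MD precedes or predicts language on the adjusted MD coefficient. GA is the essential term; PMA keeps the two analyses consistent. SES may be added as a covariate prognostic for language, but it is optional.

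Both variables are already being collected, so the change is one of wording and two model terms. With 42 infants, the model with intercept, MD, group and exposure leaves 42 − 4 = 38 residual degrees of freedom. Adding two terms leaves 36, before any clinical predictors, missing data or exclusion of multiples. That is a reason to keep the rest of the model small. The adjusted association may be weaker.
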